### Research Question

Is the SafePlan app, along with the proposed outcome measures, feasible and acceptable to patients aged 16-35 years at risk of suicide and their clinicians, in secondary-level mental health services in Ireland?

The feasibility and acceptability of using the following outcome measures in a full RCT will be assessed: the Beck Scale for Suicide Ideation (BSSI), C-SSRS, Coping Self-Efficacy Scale (CSES), Interpersonal Needs Questionnaire (INQ), and Client Service Receipt Inventory (CSRI) [38-42].

Data will be collected at baseline, post intervention, and at 6-month follow-up to determine whether the SafePlan app yielded superior outcomes on primary outcomes of suicidal ideation, suicidal behavior, and nonsuicidal self-injurious behavior when compared with the control group.

Participants: A total of 80 patients aged 16-35 years accessing secondary-level mental health services who present with current suicidal ideation, nonsuicidal self-injurious behavior, or a previous suicide attempt will be randomized to the SafePlan or control condition.Intervention: SafePlan is a safety planning mobile app informed by the paper-based SPI by Brown and Stanley [13]. Participants in the SafePlan condition will use the SafePlan app to record their safety plan in consultation with their mental health professional over an 8-week period as an adjunct to usual treatment.Comparison: The control group will receive treatment as usual (TAU) supplemented with the paper-based safety plan by Brown and Stanley [13] completed with their mental health professional.Outcome: The primary outcomes are feasibility outcomes and include the acceptability of the app to participants and clinicians, feasibility of delivery in this setting, recruitment, retention, and app use. Data collected on measures of suicidal ideation; suicidal behavior; and nonsuicidal self-injurious behavior at baseline, post intervention (8 weeks), and at 6-month follow-up will be used to compare changes in outcomes for the SafePlan condition relative to the control condition. A cost-outcome description will also be undertaken. Thematic analyses will be used to analyze the qualitative data gathered through semistructured interviews with patients and clinicians.

## Methods

### Design

The SafePlan study is a pilot RCT of SafePlan, a mobile-based safety planning app. A parallel group randomized design will be used with 1:1 patient allocation to the 2 treatment arms. In the control condition, participants will receive TAU supplemented with a paper-based safety plan. In the intervention condition, participants will use the SafePlan app to record their safety plan in consultation with their mental health professional, in addition to routine treatment. In both conditions, participants will receive appropriate care through their mental health team for an elevated risk of suicide throughout the study. Quantitative data will be collected at baseline, post intervention (8 weeks), and at 6-month follow-up (from baseline), with an additional safety check assessment at 4 weeks in both conditions.

### Participants

Participants will include patients aged 16-35 years who are currently accessing secondary-level mental health services (child and adolescent mental health services [CAMHS] or adult mental health Services [AMHS]). Participants who present with current suicidal ideation, nonsuicidal self-injurious behavior in the previous 6 months, or a previous self-reported suicide attempt will be recruited across 2 community health care organizations. Participants will be assessed by members of their mental health team, will be accessing treatment with an assigned key therapist for the entire duration of the intervention, and will provide appropriate consent (for participants aged 16-18 years, parental consent is also required). Key workers will inform potential participants who meet the eligibility criteria (Textbox 1) and for whom a SPI is clinically indicated. Participants’ psychiatric diagnoses will be recorded, but it will not be a cause for exclusion, as suicidality occurs across diagnostic categories.

Participant inclusion and exclusion criteria.
**Inclusion criteria**
Aged 16-35 yearsPresenting with current suicidal ideation, nonsuicidal self-injurious behavior in the last 6 months, or having a lifetime history of a self-reported suicide attemptCurrently accessing Health Service Executive community mental health services (child and adolescent mental health services or adult mental health services)Have been allocated a key clinician to work with the participant for the duration of the interventionThe key clinician or treating team identify that a safety plan is clinically indicatedThey were proficient in English to allow the provision of informed consent and the completion of measures in EnglishUse a smartphone and can download the SafePlan app
**Exclusion criteria**
Indicates no suicidal ideation, nonsuicidal self-injurious behavior, or previous suicide attemptsAre medically unfit for interviewAre not actively engaged with mental health servicesAre unable to provide informed consentAre outside of the specified age rangeLevel of English is not sufficient to complete outcome measures in EnglishDo not have access to a smartphone

### Clinicians

Clinicians involved in providing the intervention in both arms will be mental health service professionals and members of the patient’s multidisciplinary team who have undergone specialist training in addressing suicidality in clinical practice and the implementation of safety planning and who have completed the SafePlan technical orientation and training session. Data regarding the type of treatment received will be collected across both groups from the person’s clinical file (number of face-to-face contacts, therapeutic approach used, profession of the key clinician, and prescribed medications) and the CSRI [42].

### Sample Size

There is no established gold standard for calculating the sample size for a feasibility study, as the purpose of the study determines the sample size justification. In a systematic assessment of sample sizes in pilot and feasibility trials, Billingham et al [43] reported a median sample size of 36 participants, ranging from 10 to 300 participants. The aim of the SafePlan trial is to evaluate the feasibility of using the app as an adjunct to treatment. According to the clinician’s and service manager’s advice, a sample of 60 patients would be eligible for recruitment. With an expected 25% (20/80) dropout rate [43], a sample of 80 patients appeared adequate for the purposes of this study. Therefore, we will aim to recruit 80 patients from mental health services in Health Service Executive (HSE) West and Mid-West.

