**Methods:**

A total of 80 participants aged 16-35 years accessing Irish mental health services will be randomized (1:1) to receive the SafePlan app plus treatment as usual or treatment as usual plus a paper-based safety plan. The feasibility and acceptability of the SafePlan app and study procedures will be evaluated using both qualitative and quantitative methodologies. The primary outcomes are feasibility outcomes and include the acceptability of the app to participants and clinicians, the feasibility of delivery in this setting, recruitment, retention, and app use. The feasibility and acceptability of the following measures in a full randomized controlled trial will also be assessed: the Beck Scale for Suicide Ideation, Columbia Suicide Severity Rating Scale, Coping Self-Efficacy Scale, Interpersonal Needs Questionnaire, and Client Service Receipt Inventory. A repeated measures design with outcome data collected at baseline, post intervention (8 weeks), and at 6-month follow-up will be used to compare changes in suicidal ideation for the intervention condition relative to the waitlist control condition. A cost-outcome description will also be undertaken. Thematic analyses will be used to analyze the qualitative data gathered through semistructured interviews with patients and clinicians.

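### The Sample Size section uses 60 both as the number eligible and as the number left after dropout, so its own figures do not support the target of 80

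*Protocol article*

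**What the plan says.** The Sample Size section notes that feasibility studies have no agreed method for fixing their size, and cites a survey of pilot trials with a median of 36 participants. It then reports, on the advice of clinicians and service managers, that "a sample of 60 patients would be eligible for recruitment. With an expected 25% (20/80) dropout rate", and concludes that "a sample of 80 patients appeared adequate for the purposes of this study". The section closes with the target: "Therefore, we will aim to recruit 80 patients from mental health services in Health Service Executive (HSE) West and Mid-West".

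The abstract (Methods) gives the same 80 as the number to be randomized 1:1. So does the Research Question section: "A total of 80 patients aged 16-35 years accessing secondary-level mental health services".

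The abstract, the Research Question section and the Feasibility section all list recruitment and retention among the primary or feasibility outcomes. The section on progression to a full trial names both among the issues that the ADePT framework will examine.

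**The concern.** The paragraph gives one number two incompatible roles. In one sentence 60 is a supply figure: how many patients could be approached. In the next it is treated as what remains once 20 of 80 recruits have dropped out. Eligibility comes before recruitment and dropout comes after it, so the same 60 cannot sit at both ends.

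No powered test depends on 80. What is at stake is how the pilot's own primary outcomes are read. The Sample Size section holds the only numerical recruitment target and the only dropout expectation in the article, so readers will naturally compare the results with them. Suppose the trial recruits 55. If 60 were available, that is a very good result. If well over 80 were available, it is a poor one. As written, the article does not let anyone tell which.

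**Working it through.** **Inputs, all from the Sample Size section**
- Patients described as eligible: 60.
- Expected dropout: 25%, printed as 20/80.
- Recruitment target: 80.

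**Step 1: reproduce the target.** The standard allowance for dropout is N = n/(1 − d), where n is the number wanted after dropout and d is the dropout proportion.
- 60/(1 − 0.25) = 60/0.75 = 80, an exact match.
- The common mistaken form, n × (1 + d), gives 60 × 1.25 = 75, which does not match.
- The printed 20/80 agrees with the first form: 80 − 20 = 60.

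So the calculation is done correctly, and it uses 60 as the number retained.

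**Step 2: take 60 as labelled, the number eligible.**
- Maximum recruited: 60, which is 80 − 60 = 20 below the target.
- Target relative to the pool: 80/60 = 1.33, or 133%.
- Maximum retained at 25% dropout: 60 × 0.75 = 45, or 22 to 23 per arm. That is 60 − 45 = 15 below the number retained that the calculation implies.

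These are upper limits, because they assume that every eligible patient consents.

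**Step 3: take 60 as used, the number retained.**
- 80 must be recruited, so at least 80 must be eligible even with full consent.
- The Procedures section places identification by the team, an invitation and informed consent before randomization, and the Feasibility section plans to count those who decline. Some refusal is therefore expected.
- The documents give no consent rate. Purely as an assumed range, 80%, 70% and 50% consent would require 80/0.8 = 100, 80/0.7 = 114.3 (so 115) and 80/0.5 = 160 eligible patients.
- The article contains no eligible-pool figure other than 60 to set against any of these.

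**Step 4: look for a passage that resolves it.** The abstract and the Research Question section repeat 80 without explanation. Nowhere does the article give a larger pool, a period to which the 60 applies, or a statement that 60 is the number wanted at follow-up.

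**The case against.** The strongest reply is that this is a slip of wording. The division is right, the printed 20/80 shows what the authors had in mind, and 60 was probably meant as the number to be retained. It is also fair to say that eligibility is a flow and not a fixed stock. Teams identify patients as they present, clinician champions promote the study at weekly meetings, and the 60 might refer to a period shorter than the recruitment window. Both explanations are plausible, and the first may be the likeliest. They do not remove the problem, because they imply different achievable trials and the text does not say which applies.

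A reader might go further and infer that recruitment is bound to fail, or that 60 patients with follow-up cannot be delivered. The documents do not support that. The article sets no numerical threshold for progression. ADePT is a structured judgement across 14 issues, and the numbers approached, declining, ineligible and retained will all be reported. The 60 is never called a ceiling, and 60 retained is implied by the arithmetic but not stated as a target.

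A reader might also fault the article for not dating the 25% dropout, giving no consent rate, or not justifying 80 by the precision of a feasibility estimate. The first two are details that a condensed article commonly leaves to the full protocol. The third is a preference, given that the section openly offers a pragmatic justification. None of these is part of this point.

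**Conclusion.** The point holds in a limited form. The division is correct but is applied to a number labelled as something else, so the target of 80 is not supported by the article's own input. On the stated label, the achievable maximum is 60 recruited and about 45 retained, against 80 and an implied 60. On the other reading, 80 stands but has no estimate of eligible patients behind it.

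The figures of 60 and 45 rest on two assumptions: that 60 covers the whole recruitment period, and that everyone eligible consents. Relaxing the first could remove the shortfall, and relaxing the second would enlarge it.

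The consequence is that a shortfall against 80 could not be interpreted, in a pilot where recruitment and retention are primary outcomes and feed the progression decision. It is not that the trial must fail, nor that any test loses power. The correction is worth making before results are judged against the target.

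**What to change.** Rewrite the paragraph so that it states what 60 represents. Only the sponsor can say which of these was meant.

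- **If 60 is the number wanted at follow-up:** say so, and name the follow-up time that was intended. The article collects outcomes at 8 weeks and at 6 months and does not indicate which one the 25% refers to, so a reviewer should not choose. Keep 60/0.75 = 80 as the derivation. Give separately the services' estimate of eligible patients over the recruitment period, to show that 80 is attainable. That estimate must be at least 80 even with full consent, and higher once refusal is allowed for.
- **If 60 is the number available over the recruitment period:** restate the achievable figures as at most 60 recruited and about 45 retained, and change the 80 in the abstract and the Research Question section to match.
- **If 60 refers to a shorter period:** state the period and give the total expected over the full window.

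The cost is one rewritten paragraph and, on the second reading, a less favourable stated number. No patients are added and nothing in the design changes.

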### Setting

Participants will be recruited from community mental health services across 2 Irish community health care organizations. Participants will complete the baseline, postintervention, and follow-up measures in their mental health service setting. The orientation to the SafePlan intervention will be conducted face-to-face in the participant’s service. The control condition participants will also be introduced to paper-based safety planning face-to-face and in their service. Semistructured interviews will be conducted in the participants’ service and in the clinician’s workplace. Interviews exploring the intervention process may also be conducted by phone, depending on participant’s preferences and other safety considerations. Where face-to-face data collection is not possible owing to health concerns or other unforeseen circumstances, measures may be completed remotely. In such instances, the researcher will communicate with the participant’s key worker and members of the treating team, following the call to ensure that any information relevant to the participant’s safety is communicated to their treating team.

### Procedures

Mental health service multidisciplinary teams across both health care areas will be informed of the study and made aware of the inclusion and exclusion criteria. Team members will be asked to identify patients who are eligible to participate and for whom a safety plan is clinically indicated. Mental health service professionals will inform potential participants about the study and invite them to meet the researcher. If the patient agrees, the researcher will approach the patient, provide them with a participant information sheet, and answer any questions they may have. If the patient agrees, informed consent will be obtained by the researcher. In consenting to participate, participants will also agree to the researcher accessing their medical file notes. Information on the semistructured interviews and fidelity assessment will also be provided, and consent to future contact for this purpose will be sought. Clinicians across both community health organizations will be invited to participate in semistructured interviews to discuss their experiences of delivering the intervention.

Previously established clinician champions at each site will promote recruitment within their own teams and at weekly team meetings. Doctorate in clinical psychology students, in fulfillment of their clinical research experience and under the supervision of the principal investigator, will also support data collection across sites.

Baseline assessment measures will be administered to eligible participants who have consented to participate. Following the baseline assessment, participants will be randomized (1:1) to either the SafePlan or control condition.

An overview of the study procedures is provided in Figure 1.

**Figure 1 figure1:**
[figure not shown]
Overview of SafePlan protocol. MDT: multidisciplinary team; MHP: mental health professional; TAU: treatment as usual.

### Randomization

Randomization of participants will occur with equal probability for both groups. Participants will be stratified based on the suicide outcomes reported using the C-SSRS (Suicidal ideation/Non Suicidal Self Injurious Behavior/Suicide Attempt). Randomization will be carried out by a clinician using the sealed envelope randomization package.

### Blinding

Neither the participant nor the researcher will know the treatment arm allocation while the initial study measures are being completed. Participants will receive either the SafePlan as an adjunct to TAU or TAU supplemented with a paper-based safety plan. After randomization, both the participant and researcher will be unblinded to the participant’s allocation, which is unavoidable given the nature of the study.

Before starting the SafePlan intervention, all participants will receive a 15-minute training session on how to use the app, including downloading and password protection settings. Measures will be taken face-to-face at baseline, post intervention (8 weeks), and at 6-month follow-up. In addition to accessing TAU, phone-based check-ins will be conducted at week 4 for all participants. Participants will, therefore, have face-to-face or telephone contact with the clinician researcher at baseline assessment, 4 weeks (check-in), 8 weeks (post intervention), and 6-month follow-up. The control group participants will receive the same schedule of contacts and assessment measures.

### SafePlan Condition

The SafePlan mobile app is available to download for free and is accessed at no cost to participants. SafePlan enables participants to record their safety plan, developed with a clinician, and store it on the app to facilitate access and use outside of the clinic. Participants assigned to the SafePlan condition will meet the researcher for instructions on downloading and using the app on their personal smartphones and subsequently meet their key clinician to guide individual use of the app for safety planning. Participants will be guided by the researcher and subsequently their clinician to use SafePlan to record their safety plan in the clinic and implement the plan outside the clinic. Both patients and clinicians will be encouraged to refer to the SafePlan app during their appointments over the 8-week course of the intervention period. The SafePlan app will be used as an adjunct to treatment and will be implemented in parallel with routine community mental health care.

### Control Condition

Participants assigned to the control condition will similarly meet the researcher following enrollment for orientation to paper-based safety planning and subsequently meet their clinician to guide individualized safety planning using the safety planning template by Brown and Stanley [12]. As with the SafePlan condition, participants in the control group will be guided by the researcher and subsequently by their clinician to develop and record a safety plan using the paper-based safety plan template by Brown and Stanley [12]. Both patients and clinicians will be encouraged to refer to the paper-based safety plan during their appointments over the 8-week course of the intervention period. A paper-based safety plan will be used in addition to routine community mental health care.

### Data Collection

#### Feasibility

Feasibility is defined as the extent to which the app can be successfully used by patients attending community mental health services and by their clinician as components of standard treatment. Feasibility will be assessed in terms of recording a safety plan on the app, in-session app use, and app use over the course of treatment (as reported by patients and clinicians). Quantitative data from patients will be collected at baseline, post intervention (8 weeks), and at 6-month follow-up; qualitative data from patients and clinicians will be collected through semistructured interviews. Table 1 presents the study data collection timelines. Psychometric measures will be administered at multiple time points to identify possible differences in the outcomes over the course of the study.

Feasibility outcomes will include the acceptability of the intervention to participants and clinicians, feasibility of delivery in this setting, recruitment, retention, and app use. Quantitative data on the number of potential patients who were approached and who declined, who were not eligible, and who were retained will be recorded and presented in the Consolidated Standards of Reporting Trials diagram for the study.

This study will be conducted in line with the MRC guidelines on the evaluation of complex interventions [37], with data collected via quantitative and qualitative methods.

Participants who consent to be contacted for the qualitative element of the study will be invited to participate in a one-to-one interview about their experiences of the intervention and of study procedures. The interviews will be conducted face-to-face at the university or health service site, and where necessary, participants will be given the additional option of a telephone interview. In the case of telephone interviews, verbal consent will be audio-recorded at the beginning of the interview.

Mental health professionals (n=12) directly involved in participants’ care and in delivering the intervention (eg, CAMHS/AMHS multidisciplinary team members) will be invited to participate in the semistructured interviews. Interviews will focus on the feasibility of the intervention and the acceptability of the study and intervention procedures, including experienced or perceived barriers and facilitators, intervention “fit” within the setting, and suggestions for improvement.

**Table 1 table1:** Study data collection timelines.

	Demographic information	Clinical file data	Client Service Receipt Inventory	Columbia Suicide Severity Rating Scale	Beck Scale for Suicide Ideation	Interpersonal Needs Questionnaire	Coping Self-Efficacy Scale	Safety plan completion	App use (self-report)	Paper plan use (self-report)
Baseline SafePlan condition	✓	✓	✓	✓	✓	✓	✓			
Baseline control condition	✓	✓	✓	✓	✓	✓	✓			
4-week check-in SafePlan condition				✓				✓	✓	
4-week check-in control condition				✓				✓		✓
8-week SafePlan condition			✓	✓	✓	✓	✓	✓	✓	
8-week control condition			✓	✓	✓	✓	✓	✓		✓
6-month SafePlan condition			✓	✓	✓	✓	✓		✓	
6-month control condition			✓	✓	✓	✓	✓			✓

